## Abstract

**Background:**

A stroke is described by the World Health Organization as “a clinical syndrome with rapidly developing symptoms that consist of a focal (or global, in a situation of coma) disruption of cerebral function that lasts more than 24 hours or leads to mortality without a known cause other than a vascular origin”. Stroke is the most prevalent cause of impairment and mortality on a global scale. Modified constraint-induced movement therapy (mCIMT) is an approach to therapy for motor disabilities that involves constraining the movements of the nonparetic limb, diligent practice and behaviour modification to extend the time the paretic limb is utilized for daily tasks. The motor relearning program (MRP) method involves many aspects of motor learning theory and is helpful in providing instructions for retraining practical skills (including walking, standing and sitting in balance and transferring abilities). So, the objective of this study is to assess the impact of the MRP and mCIMT on balance and gait in sub-acute hemiplegic stroke patients.

**Methods:**

In this study, each group will consist of 17 people in total. The randomization procedure will be conducted using a computer-generated random number system. For sample distribution, we will use the sequentially numbered opaque sealed envelope technique. Outcome measures will be as follows: Berg balance scale, Dynamic gait index, Trunk impairment scale, Functional reach test, 10 Meter walk test and Fall efficacy test. Each patient will be evaluated prior to and during treatment at baseline and six weeks later.

**Conclusions:**

There is sufficient evidence to derive the conclusion that the functional mobility and balance of stroke victims can be improved with physiotherapy. Therefore, this study will try to seek the comparison of mCIMT (group A) and MRP (group B) in sub-acute stroke subjects and compare the two regimes to determine which one will be superior.

**Registration:**

CTRI (
CTRI/2023/05/052674; 16/05/2023).

## Introduction

Stroke, which is deemed by the World Health Organization (WHO) to be the “quickly growing clinical evidence of a permanent (or worldwide) brain function impairment with sign and symptoms lasting 24 hours or more or causing mortality with no apparent cause other than the vascular origin”.
^
1
^ Stroke incidence ranges from 105 to 152/100,000 per year, making it the third most prevalent cause of impairment and the second-leading cause of mortality worldwide.
^
2
^
^,^
^
3
^ In India, the prevalence of stroke considerably rises with age; compared to younger persons, the risk is higher for those over 55 years old and lower for those between 45 and 54 years old (0.80%
*vs.* 1.97%, respectively). Stroke risk is higher in men than in women. African Americans, Hispanics, and Americans have a higher risk of stroke compared to other races. Americans are more likely to have a stroke.
^
4
^ Stroke is divided into two distinct subtypes based on its aetiology: ischemic and haemorrhagic. The ischemic type of stroke, which affects 85% of patients, arises whenever the vascularity of the brain tissue is damaged as the blood clot blocks or plugs a blood vessel in the brain. However, 15% of acute strokes are haemorrhagic strokes, which are brought on by a burst blood vessel or an abrupt haemorrhage. Subarachnoid and intracerebral haemorrhage are the two main forms of haemorrhagic attacks.
^
5
^

There are numerous causes of stroke. Common risk factors include smoking (12%), heredity, hypertension, diabetes mellitus, high cholesterolemia (15%) and lack of physical activity.
^
4
^ Alcohol consumption that is mild to moderate carries a slightly lower risk of ischemic stroke, however higher drinking significantly boosts the risk.
^
6
^ Common stroke problems include gait impairment that makes it difficult to maintain postural alignment as well as stiffness, fatigue, and loss of balance on the affected side. One of the most frequent problems following a stroke is paralysis. Usually, opposing the brain side of the body that has been harmed by a stroke undergoes the paralysis. It can affect the overall side of the body, the face, upper limb, lower limb or even one of the legs. Hemiplegia refers to this type of unilateral paralysis. There are several anatomical and functional abnormalities that are followed by hemiplegia. These people frequently have functional mobility and balance issues as a result of their movement paralysis.
^
7
^ Balance is the ability to maintain the line of gravity within the base of support with minimal postural sway. Balance impairment is characterised by short supporting time and differences between two sides of the body and slow walking speed, which may increase the risk of falls. Without using more resources, a planned program can considerably raise documented patient activity levels during inpatient stroke therapy.

The main goal of stroke treatment is to promote activity in daily life (ADL) independence while restoring function.
^
8
^ There are numerous physiotherapy approach treatments for stroke, including body weight supported treadmill training, electromechanical-assisted training, virtual reality therapy, constraint-induced movement therapy, motor relearning program, robot-assisted training, mirror therapy and proprioceptive neuromuscular facilitation. All methods for restoring voluntary control and mobility after a stroke operates according to its own principles.
^
9
^ Major studies have revealed that muscle weakness is the main thing preventing physical function from recovering.
^
9
^ Conventional exercises are ones that are performed all around the world. These include exercises such as passive motion, exercise at the gym, gait training, electrical stimulation, and functional re-education.
^
10
^ Modified constraint-induced movement therapy (mCIMT) is a type of therapeutic intervention for those with motor disabilities. The established method for treating the paretic upper limb enhances the functional usage by preventing “learned disuse” that occurs after a stroke.
^
11
^
^,^
^
12
^

Three main elements of mCIMT include the use of repetitive, structured, practice-intensive therapy in the more paretic limb, constraint of the non-paretic limb and a variety of behavioural strategies that translate improvements made in a clinical setting to everyday life. Recently, mCIMT has also been used to the paretic lower limb with the goal of improving neurological function and prevent “learned misuse”. One of the rehabilitation techniques utilised predominantly with the post-stroke population is the motor relearning program (MRP). This technique incorporates several elements of motor learning theory and includes practical advice for retraining practical abilities (such as a balanced sitting position, sitting and standing, skill transfer, and walking).
^
13
^ With good feedback and practise, this approach focuses on the growth of active movement control and task-specific learning. It is less frequently encountered to use facilitation tactics in preference for verbal direction, demonstrations and manual recommendation.
^
14
^

Three main elements of mCIMT include the use of repetitive, structured, practice-intensive therapy in the more paretic limb, constraint of the non-paretic limb and a variety of behavioural strategies that translate improvements made in a clinical setting to everyday life. Recently, mCIMT has also been used to the paretic lower limb with the goal of improving neurological function and prevent “learned misuse”. One of the rehabilitation techniques utilised predominantly with the post-stroke population is the motor relearning program (MRP). This technique incorporates several elements of motor learning theory and includes practical advice for retraining practical abilities (such as a balanced sitting position, sitting and standing, skill transfer, and walking).
^
13
^ With good feedback and practise, this approach focuses on the growth of active movement control and task-specific learning. It is less frequently encountered to use facilitation tactics in preference for verbal direction, demonstrations and manual recommendation.
^
14
^

### Aims and objectives

1.To study the effect of mCIMT in addition to conventional therapy on balance (using the Berg Balance Scale (BBS)) and gait (using the Dynamic Gait Index (DGI)) in sub-acute hemiplegic stroke.2.To study the effectiveness of MRP along with conventional therapy on balance (BBS) and gait (DGI) in sub-acute hemiplegic stroke.3.To compare mCIMT and the MRP in improving balance and gait in sub-acute hemiplegic stroke patients along with conventional therapy.

### Trial design

A single-centre, two arm, parallel group, comparative open labelled superiority trial will be conducted.

## Methods

### Protocol

The model consent form, data collection form and schedule of enrolment, interventions and assessments can be found as
*Extended data.*
^
24
^ This protocol adheres to the SPIRIT guidelines.
^
25
^

After gaining clearance from the Institutional Ethics Committee (IEC) of Datta Meghe Institute of Higher Education and Research (Deemed to be University), participants will be enrolled from the Physiotherapy Outpatient Department of Acharya Vinoba Bhave Rural Hospital Sawangi, Meghe, Wardha, Maharashtra. A total of 34 participants will be made aware of the study’s objectives and procedures and will be asked to sign written patient consent forms. All hemiplegic stroke patients who meet the inclusion and exclusion parameter will be included in the study. They will be further separated into Group A and Group B by means of simple random selection. Each group will consist of 17 people in total. The randomization procedure will be conducted using a computer-generated random number system. For sample distribution, we will use the sequentially numbered opaque sealed envelope technique. There will be no blinding procedure in this study. The principal investigator will generate allocation, enrol participants and assign participants to interventions. A departmental committee made up of the Post Graduate (PG), Guide, the Head of Department (HOD), the Principal of the Ravi Nair Physiotherapy College (RNPC) and a member of the Research Guidance Cell will oversee the project. Through routine treatment sessions, we will make sure that the patients follow the suggested treatment plan closely. If necessary, individuals will receive counselling or telephone reminders about their therapy appointments. Prior to and following the analysis, the outcome measures will be assessed. The study’s outcome indicators are as follows: The BBS, DGI, Trunk Impairment Scale (TIS), Functional Reach Test (FRT), 10 Meter Walk Test (10MWT) and Fall Efficacy Scale (FES) along with conventional treatment for balance and gait. mCIMT will be given in Group A in addition to conventional therapy, whereas Group B will receive the MRP in addition to conventional therapy.
Figure 1 and
Figure 2 depict the study design.

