### Sample size calculation

We estimated the sample size using a power analysis with 80% power and 5% Type 1 error for the main variables. The BBS score, in comparison to the difference in mean score pre and post treatment for mCIMT group from baseline to end visits. For the study, we used the previously determined effect size difference in percentage from the RCT.
^
22
^ Formula using mean difference:

$$n1=n2=2\frac{{\left(Z_{\alpha }+Z_{\beta }\right)}^{2}\sigma^{2}}{{\left(\delta \right)}^{2}}$$
Primary Variable (BBS)

Mean ± SD (Pre) result on BBS for mCIMT = 48.8 ± 4.7

Mean ± SD (Post) result on BBS for mCIMT = 52.5 ± 3.5

Difference = 3.7

Pooled std. dev. = (4.7 + 3.5)/2 = 4.1

$$\text{N1}=2^{*}\left[{\left(1.64+0.84\right)}^{2}{\left(4.1\right)}^{2}\right]/{\left(3.7\right)}^{2}=15$$

Considering 10% dropout = 2

Total samples required = 15 + 2 = 17 per group.

Total sample size required = 15

Notations:

$$Z_{\alpha }=\text{1.64 bat 5\% l.o.s. at both sides total 10\% type I error}$$

α=Type I error at 5%

$Z_{\beta }=0.84\;\left(1-\beta \right)=\text{Power at}\;80\%$

σ=std.dev=0.5pooledstd.dev

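### Unrestricted simple randomisation does not guarantee the fixed 17 per group, and the allocation list, however restricted, is open to the principal investigator who generates it

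*Protocol article*

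**What the plan says.** The Protocol section under Methods gives the total first ("A total of 34 participants will be made aware of" the study and asked to consent), then the method: "They will be further separated into Group A and Group B by means of simple random selection". The next sentence fixes the result: "Each group will consist of 17 people in total". The sequence comes from random numbers ("The randomization procedure will be conducted using a computer-generated random number system") and concealment from envelopes ("For sample distribution, we will use the sequentially numbered opaque sealed envelope technique"). No block, permutation or other restriction is mentioned.

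The Sample size calculation section arrives at the same number: "Total samples required = 15 + 2 = 17 per group".

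On roles and blinding, the Protocol section states "The principal investigator will generate allocation, enrol participants and assign participants to interventions" and "There will be no blinding procedure in this study". The Data collection methods section adds that the principal investigator delivers the study treatment, supervised by the guide. The Trial design section describes a single-centre, open-label trial.

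**The concern.** Simple randomisation leaves arm sizes to chance, so the stated method and the stated arm sizes agree only by luck. Two readings are possible, and each leaves something to settle.

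- **The method is simple as written.** The 17 per group is then an expectation, not a fact of the design, and should not be stated as fixed.
- **The split is held at 17/17.** Some restriction is then in use that the article does not describe. Any such restriction makes the last allocations certain to someone who counts the arms.

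The second reading matters here because one unblinded person makes the list, enrols, assigns and treats. A person who knows or can guess the next allocation can, even without intending to, influence who is enrolled next. Both primary outcomes, the Berg Balance Scale and the Dynamic Gait Index, are scored by an observer, and with 34 patients a few selectively placed ones could shift a mean.

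**Working it through.** **Inputs.** Total 34 and 17 per group (Protocol section). Difference 3.7, SD 4.1, z-values 1.64 and 0.84, 10% dropout taken as 2 (Sample size calculation).

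**1. The plan's own figure.** n = 2 × (1.64 + 0.84)² × 4.1² / 3.7² = 15.10, stated as 15. Adding 2 gives 17 per group and 34 in total. The stated size reproduces, apart from rounding 15.10 down instead of up.

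**2. Arm sizes under simple randomisation.** The number in Group A is binomial with 34 trials and probability 0.5.

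- P(17/17) = C(34,17) / 2³⁴ = 2,333,606,220 / 17,179,869,184 = 0.136

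| Split | Probability |
|---|---|
| exactly 17/17 | 13.6% |
| 18/16 or worse | 86.4% |
| 19/15 or worse | 60.8% |
| 20/14 or worse | 39.2% |
| 22/12 or worse | 12.1% |

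**3. What imbalance costs in power.** Arms of size a and b carry the information of 2ab/(a + b) per arm. Power on the plan's basis (z of about 1.64, normal approximation, all 34 analysed) is Φ(3.7 / [4.1 × √(1/a + 1/b)] − 1.645).

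| Split | Equivalent equal arm | Power |
|---|---|---|
| 17/17 | 17.0 | Φ(2.631 − 1.645) = 83.8% |
| 20/14 | 560/34 = 16.5 | Φ(2.590 − 1.645) = 82.8% |
| 22/12 | 528/34 = 15.5 | Φ(2.515 − 1.645) = 80.8% |

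Averaged over all binomial splits, power is 82.8%, so the average loss is 83.8 − 82.8 = 1.0 percentage point. Whether z = 1.64 is the right value is a separate question and does not affect this comparison.

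**4. How much of the list is determined if 17/17 is forced.** The article does not say how, or whether, this would be done, so both common ways are shown.

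- *One random ordering of 17 A and 17 B.* P(last L allocations identical) = 2 × C(34 − L, 17 − L) / C(34,17). The last is always determined, the last two or more with probability 48.5%, the last three or more 22.7%. The mean is 34/18 = 1.9.
- *Fair coin, arm closed when it reaches 17.* The mean forced tail is 34 × 0.1358 = 4.6, with five or more forced in 45.8% of sequences.

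**5. How guessable each method is.** Suppose someone who sees all past allocations always guesses the smaller arm, and guesses at random when the arms are level. Expected correct guesses out of 34:

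| Method | Correct | Share |
|---|---|---|
| unrestricted simple randomisation | 17.0 | 50% |
| coin, arm closed when full (simulated) | 19.3 | 57% |
| random ordering of 17 + 17 (exact) | 20.2 | 59% |
| random blocks of 2, 4 and 6 (simulated) | 24.0 | 71% |

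**6. The list's author.** Steps 4 and 5 describe someone who sees only past allocations. The article has the principal investigator generate the sequence, and that person can know all 34 under any method. Opaque envelopes do not conceal a list from whoever made it.

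**The case against.** The strongest reply is that the article's label is loose. A computer-generated random ordering of 17 A and 17 B in numbered envelopes fits every operational sentence in the Protocol section and gives 17/17 every time. It is also fair to say that an article may leave block details to the full protocol. The first part stands to this extent: it would be wrong to say that the method cannot deliver 17 per group. The second part does not dispose of the point. The article is not silent on method: it names one, and the one it names does not fix the arm sizes.

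A reader might infer three stronger things that the document does not support.

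- **That the end of the list will be forced.** The article nowhere describes closing an arm. The 4.6 figure assumes such a rule, and a random ordering gives 1.9. Both are conditional.
- **That an arm below 15 means the sample size requirement is missed.** The 15 applies to equal arms. A 20/14 split is worth 16.5 per arm and 22/12 is worth 15.5, both above 15 before dropout. The power loss is small.
- **That small permuted blocks are the natural remedy.** In an unblinded single-centre trial, blocks of 2, 4 and 6 are the most guessable of the four methods compared, and hiding block sizes from the enrolling person is impossible while that person makes the list.

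**Conclusion.** The point holds as an inconsistency with a concealment consequence, not as a power problem. As written, the allocation method misses the stated 17/17 in 86% of sequences and gives 20/14 or worse in 39%, at an average cost of about 1 percentage point of power. If equality is forced, between about 1.9 (random ordering) and 4.6 (arm closed when full) allocations are determined on average. The larger weakness is that the principal investigator's control of the list exposes all 34, whichever method is used.

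The binomial figures assume 34 independent fair allocations. The power figures take the plan's difference, SD and z-value as given. The forced-tail figures rest on procedures that the article does not state. That selection would actually occur is not shown; the design leaves it open.

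**What to change.** 1. Replace the reference to simple random selection with a restricted 1:1 computer-generated list totalling 17 per arm. Suitable forms are one random ordering of 17 A and 17 B, or large blocks of varying size whose lengths sum to 34. Avoid small blocks such as 2.
2. Have the list generated, and sealed in the sequentially numbered opaque envelopes already planned, by someone who does not enrol, assign or treat. The statistician mentioned under Data management, or a departmental committee member with no part in enrolment or treatment, would serve. The principal investigator should not see the list.
3. If the sponsor prefers to keep simple randomisation, restate 17 per group as an expected size. Step 2 is needed either way.

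The cost is one or two sentences, a different list-generation command and a little of an existing colleague's time. No extra patients are needed. The small downside is that a restricted list is somewhat more guessable than simple randomisation (20.2 against 17.0 of 34 for the single ordering). The article says the study has not begun, so this can be done before the first patient. Its Protocol amendments section says no further changes can be made, so the correction would need to be taken to the ethics committee and the registry entry checked against it.

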### Data collection methods

Before group allocation, screening of the participants as per the inclusion and exclusion criteria will be carried out. This will be followed by baseline assessment of the outcome measures as mentioned. All participants will undergo the randomization process and are allocated into either group A or Group B. The intervention will be administered for an hour daily, five days per week for six weeks. The post intervention data for the outcomes will be recorded after the last intervention session day. The data will be compiled and analysed for studying the results. The study interventions will be administered by the principal investigator under the supervision of the guide throughout the duration of the study. The patients will be instructed and reminded of the sessions in advance through messages sent to their mobile phones so that adherence to the study is ensured. Furthermore, if the patient misses their sessions due to any reason, the standby days from the week will be utilized such that the patient receives a total of 30 sessions of intervention in the six week duration.

As per in the sample size calculation we have given a 10% dropout rate so that it does not interfere with the results of our study.

The data collection forms can be found as
*Extended data.*
^
24
^

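### The principal investigator generates the sequence, enrols, assigns and treats, so sealed envelopes cannot conceal the allocation from the person who enrols

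*Protocol article*

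**What the plan says.** The protocol article describes allocation in Methods, Protocol. The sequence comes from a computer: "The randomization procedure will be conducted using a computer-generated random number system". Concealment rests on envelopes: "For sample distribution, we will use the sequentially numbered opaque sealed envelope technique". Three roles then go to one person: "The principal investigator will generate allocation, enrol participants and assign participants to interventions".

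Data collection methods adds a fourth: "The study interventions will be administered by the principal investigator under the supervision of the guide throughout the duration of the study". Interventions likewise identifies the therapist as the principal investigator.

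On the type of randomisation, patients are to be "separated into Group A and Group B by means of simple random selection", and "Each group will consist of 17 people in total". On masking: "There will be no blinding procedure in this study".

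Data collection methods places screening and baseline assessment before allocation. The Protocol section says that all patients who meet the criteria will be included. Nothing in the article gives preparation or custody of the list or the envelopes to anyone else.

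**The concern.** Allocation concealment means that whoever decides on a patient's entry cannot know the next assignment. Envelopes achieve this only when someone else has made the list and filled them. Here the person who enrols is the person who generated the sequence.

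If the next assignment is known, it can influence whether a borderline patient is judged eligible, or when a patient is entered. Some criteria need judgement, for example the ability to understand and follow instructions. The arms could then differ in expected recovery before treatment starts. Adjustment for measured baseline variables can reduce a bias that runs through those variables. It cannot remove one that runs through prognosis nobody recorded. With 17 patients per arm, a few such decisions could move the comparison.

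**Working it through.** **1. Roles side by side.**

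- Generates the sequence: principal investigator (Methods, Protocol).
- Enrols: principal investigator (same sentence).
- Assigns: principal investigator (same sentence).
- Treats: principal investigator (Interventions; Data collection methods).
- Prepares or holds the list and envelopes: nobody else is named.
- Oversight: the departmental committee has no stated part in randomisation, and the data monitoring committee is led by the principal investigator (Monitoring).

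No step in this chain places the sequence out of the enroller's reach.

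**2. The plan's own figure.** Sample size calculation gives 2 × (1.64 + 0.84)² × 4.1² / 3.7² = 15.10, stated as 15, plus 2 for dropout = 17 per group. The 17 per group is used below as context only; this point does not depend on how it was derived.

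**3. How much of the sequence can be known.** For a list fixed at n per arm, the expected number of correct guesses for someone who always guesses the arm with more places left is E = n − 1/2 + 1/(2P), where P = C(2n, n)/2^(2n).

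- The enroller made the list: up to 34 of 34 assignments (100%).
- Hidden list, independent coin tosses: 17 of 34 (50%).
- Hidden list fixed at 17/17 (n = 17): P = 0.1358, so E = 16.5 + 1/0.2717 = 20.18 of 34 (59%).
- Hidden list in blocks of 4 of known size (n = 2): P = 6/16, so E = 1.5 + 1.333 = 2.83 of 4 (71%).
- Hidden list in blocks of 2 of known size (n = 1): P = 1/2, so E = 0.5 + 1 = 1.5 of 2 (75%).

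Small blocks would therefore give more away to an enroller who treats every patient and sees every past allocation.

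**4. Simple randomisation against 17 per group.** If the wording means independent coin tosses, the chance of exactly 17/17 is the P above, 0.136. If it means drawing 17 of 34 at random, 17/17 is certain. The text does not say which.

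**5. Possible consequence (assumption).** The article gives no size for a selection effect, so a range is shown. Let d be a difference between arms in expected BBS change caused only by selection. Take no true treatment effect, SD 4.1, 17 per arm and a two-sided 5% test in normal approximation. The standard error is 4.1 × √(2/17) = 1.406, and the false-positive rate is Φ(d/1.406 − 1.96) + Φ(−d/1.406 − 1.96).

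- d = 0.5: about 6.5%
- d = 1: about 11%
- d = 2: about 30%

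The SD of 4.1 is the article's average of a pre-treatment and a post-treatment SD, not an SD of change. The rates are indicative only.

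**The case against.** The best defence is procedural. Screening and baseline assessment come before allocation, and every patient who meets the criteria is to be included. Both limit discretion. Neither stops a person who made the list from knowing the next assignment while judging a criterion or timing an entry, and no independent eligibility check is described. The article does not say outright that the principal investigator does the screening; that is a fair inference from the enrolling role. One could also suppose that the list is printed and sealed unseen, but nothing says so. An article condenses a fuller protocol, but this role assignment is explicit, so a fuller text could rescue it only by contradicting it.

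Other parts of the defence stand, and they rule out stronger readings that a reader might infer:

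- **That selection bias is certain.** The document shows an opportunity, not an event. The envelopes may still conceal allocations from patients and other staff.
- **That lack of blinding is why concealment fails.** An open-label trial can conceal its sequence perfectly well. Unblinded scoring of the observer-rated BBS and DGI is a separate matter of detection bias. The article does not say who scores them.
- **That 17 per group is unattainable or damaging.** A random draw of 17 from 34 achieves it. Even a 20/14 split would leave 2 × 20 × 14 / 34 = 16.5 effective patients per arm. The wording is loose, but it is not itself a source of selection bias.
- **That a baseline shift in BBS carries straight into the result.** The outcome is change in BBS, so steering would have to act on expected improvement.

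**Conclusion.** The point holds as an unprotected concealment procedure. By the article's own statement, one person generates the sequence, enrols and assigns, and that person also treats. Envelopes cannot hide a sequence from its author. This is a stated rule rather than a detail left to a fuller document, and it should be changed before enrolment begins, because it cannot be put right afterwards.

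The firm part of its size is the possible foreknowledge: up to 34 of 34 assignments, against about 20 of 34 by best guessing if an unblocked 17/17 list were held elsewhere. The false-positive rates of 6.5% to 30% rest on assumed shifts of 0.5 to 2 BBS points and on an approximate SD. They show what is at stake, not what will happen. The sample size does not change.

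**What to change.** Before the first patient:

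1. Have someone already named in the article who neither enrols nor treats generate the list and prepare and hold the envelopes. The statistician (Data management) or the Research Guidance Cell member (Methods, Protocol) would serve.
2. Release the next envelope only after consent, eligibility and baseline assessment are recorded for that patient.
3. State the randomisation type so that it agrees with 17 per group, for example a concealed random permutation of 17 A and 17 B. This raises best-guess predictability from 50% to about 59% compared with coin tosses, a modest price for equal groups. Small blocks are not required and would raise it further.

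The cost is a small amount of an existing team member's time and a protocol amendment. Protocol amendments says that further changes are no longer possible after the approvals already given, so the committees would have to agree. Study status confirms that the trial has not begun, so the change is still in time. Treatment and sample size are unaffected.
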